### Randomization and allocation concealment

2.4

Eligible participants will be randomized using a computer-generated random number sequence created with Python (version 3.10 or higher). The sequence with a 1:1 allocation ratio by an independent statistician who is not involved in participant recruitment or intervention. Allocation will be concealed using sequentially numbered, opaque envelopes. Investigators responsible for recruitment and intervention will be unblinded, while outcome assessors and data analysts will remain blinded.

Figure 1 presents the research flow.

**Figure 1 F1:**
[figure not shown]
Study flow chart.

### Interventions

2.5

#### Control group: conventional medication

2.5.1

Participants will receive montelukast sodium chewable tablets: 5 mg once daily (bedtime).

Acute exacerbations during the trial will be managed with salbutamol aerosol or budesonide plus terbutaline nebulization, in accordance with clinical guidelines.

#### Intervention group: conventional medication plus pediatric tuina

2.5.2

Participants will receive the same medication as the control group, plus standardized pediatric Tuina. The Tuina protocol is based on TCM theory for “lung-spleen-kidney deficiency” (19) and includes:

Basic acupoints and techniques:

- Tonifying Spleen Meridian (300 rotations) [Figures 2A, B], Lung Meridian (300 rotations) [Figures 2C, D], Kidney Meridian (300 rotations) [Figures 2E, F].- Circulating Inner Eight Trigrams (300 times) [Figures 3A, B].- Kneading Tiantu (20 times) [Figures 3C, D], Danzhong (20 times) [Figures 3E, F], Yongquan (20 times) [Figures 4A, B].- Rubbing the costovertebral region (50 times) [Figures 4C, D].- Kneading Feishu (50 times) [Figures 4E–G], Pishu (50 times) [Figures 5A–C], Shenshu (50 times) [Figures 5D–F].- Pinching the spine (5 times) [Figures 5G–I].

**Figure 2 F2:**
[figure not shown]
Spleen meridian, lung meridian, and kidney meridian. **(A)** spleen meridian, **(B)** pushing spleen meridian, **(C)** lung meridian. **(D)** pushing lung meridian, **(E)** kidney meridian, **(F)** pushing kidney meridian.

**Figure 3 F3:**
[figure not shown]
Inner eight trigrams, Tiantu and Danzhong. **(A)** Inner eight trigrams, **(B)** transporting inner eight trigrams, **(C)** Tiantu, **(D)** kneading Tiantu, **(E)** Danzhong, **(F)** kneading Danzhong.

**Figure 4 F4:**
[figure not shown]
Yongquan, costovertebral region, and Feishu. **(A)** Yongquan, **(B)** kneading Yongquan, **(C)** costovertebral region, **(D)** twisting and rubbing costovertebral region, **(E)** Feishu, **(F)** kneading Feishu (back side), **(G)** kneading Feishu (lateral side).

**Figure 5 F5:**
[figure not shown]
Pishu, Shenshu, and spine. **(A)** Pishu, **(B)** kneading Pishu (back side), **(C)** kneading Pishu (lateral side), **(D)** Shenshu, **(E)** kneading Shenshu (back side), **(F)** kneading Shenshu (lateral side), **(G)** spine (back side), **(H)** pinching spine, **(I)** pinching spine (lateral side).

Additional movie files show this in more detail (see S1–S12 Movies).

Frequency and duration: 3 sessions/week for 4 weeks (total 12 sessions), each lasting 15–20 min. Tuina will be performed by certified therapists trained in the standardized protocol.

The anatomical localization of acupoints for pediatric Tuina strictly follows national standard as shown in Table 2 (20).

**Table 2 T2:** Location of acupoints.

Acupoint	Location
Spleen meridian	The thumb ball, or the line from the tip to root on the radial border of thumb.
Lung meridian	The fingertip of the ring finger.
Kidney meridian	The fingertip of the little finger.
Inner eight trigrams	Taking palm center as the center, draw a circle with the radius from the center to the point at inner 2/3 of distance between palm center and transverse crease of middle finger root. Inner Eight Trigrams indicates the area within the circle.
Tiantu	In the depression, 0.6 cun superior to the midpoint on upper border of sternal notch, on conception vessel.
Danzhong	On the sternum, at the midpoint between two breasts.
Yongquan	On the sole of the foot, in the depression at the anterior part when the foot is curled. It is approximately located at the junction of the anterior 1/3 and posterior 2/3 of the line connecting the web margin tip between the 2nd and 3rd toes to the heel.
Costovertebral region	Hypochondriac regions from axillary line to ST 25 (tiān shu).
Feishu	1.5 cun lateral to lower border of the spinous process of the 3rd thoracic vertebra.
Pishu	1.5 cun lateral to lower border of the spinous process of the 11th thoracic vertebra.
Shenshu	1.5 cun lateral to lower border of the spinous process of the 2nd lumbar vertebra.
Spine	The straight line between DU 14 (dà zhui) and DU 1 (cháng qiáng).

### Outcome measures

2.6

#### Primary outcome

2.6.1

Quality of life: PRQLQ score (higher scores indicate poorer quality of life) at T0, T1, T2, T3, T4 and T5.

#### Secondary outcomes

2.6.2

TCM symptom scores: assessing nasal (e.g., congestion, runny nose) and respiratory (e.g., cough, wheezing) symptoms, scored 0–3 (0 = absent, 3 = severe) (21).Asthma control: C-ACT for 6–11 years old, ACT for 12–14 years old (higher scores indicate better control).

#### Safety outcome

2.6.3

Adverse events (AEs) will be continuously monitored. Participants will be explicitly asked about any new or worsening symptoms at each treatment session and follow-up assessment. AEs specifically related to pediatric Tuina include, but are not limited to: intolerable pain, skin irritation, hematoma, bleeding, skin allergy, sweating, syncope, or dizziness. All AEs occurring during the trial will be assessed and documented in case report forms. Investigators will record detailed information on treatment measures, extent, duration, and the date of the AE. In the event of a serious AE, investigators must report it to the Ethics Committee of Shanghai Municipal Hospital of Traditional Chinese Medicine. The Ethics Committee will decide whether to withdraw a participant experiencing an AE, and will conduct audits every three months.

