**Methods:**

A total of 92 children aged 6–14 years with CARAS in remission will be randomly assigned (1:1) to either the control group (conventional medication) or the intervention group (conventional medication plus pediatric Tuina). The intervention will be administered three times weekly for 4 weeks, followed by a 24-week follow-up. The primary outcome measure is the Pediatric Rhinoconjunctivitis Quality of Life Questionnaire (PRQLQ) score. Secondary outcomes include the Childhood Asthma Control Test (C-ACT) / Asthma Control Test (ACT) score and traditional Chinese medicine (TCM) symptom scores. Safety will be assessed by monitoring any adverse events during the treatment period.

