### Study design

2.1

This is a single-center, randomized, superiority, parallel-group controlled trial with a 1:1 allocation ratio. This is a single-center trial. All participant recruitment, intervention, and assessment procedures will be conducted at the Shanghai Municipal Hospital of Traditional Chinese Medicine, Shanghai, China. The study will consist of a 4-week intervention phase and a 24-week follow-up phase. Outcome assessments shall be conducted at baseline (T0), following the intervention (T1, week 2; T2, week 4), and during follow-up periods (T3, week 8; T4, week 12; T5, week 28). Assessors will remain blinded to group allocation to mitigate potential bias.

Table 1 presents the study schedule.

**Table 1 T1:** Timeline for the study protocol.

	Trial period						
	Enrollment		Post-randomization		Follow-up		Close-out
Timepoint	–T1 to T0	T0	T1	T2	T3	T4	T5
Enrollment	
Eligibility screen	X						
Informed consent	X						
Randomization		X					
Intervention or comparator							
Intervention group: conventional medication plus pediatric Tuina		X	X	X			
Comparator group: conventional medication		X	X	X			
Assessments							
Baseline		X	X	X	X	X	X
PRQLQ		X	X	X	X	X	X
C-ACT/ACT		X	X	X	X	X	X
TCM symptom scores		X	X	X	X	X	X
Safety evaluation		X	X	X			

PRQLQ, pediatric rhinoconjunctivitis quality of life questionnaire; C-ACT, childhood asthma control test; ACT, asthma control test.

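### Adverse events are asked about at Tuina sessions that controls do not have, which tilts recorded mild events toward the Tuina arm; separately, the safety window is stated inconsistently

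*Protocol article*

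**What the plan says.** **How events are elicited.** Section 2.6.3 (Safety outcome) sets the only active enquiry procedure in the article: "Participants will be explicitly asked about any new or worsening symptoms at each treatment session and follow-up assessment". The same section says in general terms that monitoring is continuous.

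**Who has sessions.** Section 2.5.2 gives the Tuina schedule as "3 sessions/week for 4 weeks (total 12 sessions), each lasting 15–20 min". Section 2.5.1 gives controls a once-daily oral tablet and describes no sessions for them. On the intervention arm, Section 2.5.2 says: "Participants will receive the same medication as the control group, plus standardized pediatric Tuina". The manual therapy, with its visits, is thus the whole planned difference between the arms.

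**Visits common to both arms.** Section 2.1 sets T0 at baseline, T1 and T2 at weeks 2 and 4, and T3, T4 and T5 at weeks 8, 12 and 28.

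**The period in which safety is assessed.** Three places address this:
- Abstract, Methods: "Safety will be assessed by monitoring any adverse events during the treatment period".
- Table 1, row "Safety evaluation": marks at T0, T1 and T2 only. The rows for the quality-of-life, asthma-control and TCM symptom scores are marked at all six time points.
- Section 2.6.3: enquiry at follow-up assessments too, and "All AEs occurring during the trial will be assessed and documented in case report forms".

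**The concern.** There are two separate issues.

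The first is that how often a child is asked depends on the arm. Several of the Tuina-related events named in Section 2.6.3, such as sweating, dizziness and skin irritation, can be mild and short-lived. A child asked every two or three days is more likely to mention such an event than a child asked after two weeks. If all reports are pooled, the Tuina arm would show more events with no true difference in risk, and a true excess among controls could be masked. Section 2.4 adds that staff responsible for the intervention are unblinded. If they do the asking at sessions, the extra reports come from people who know the allocation.

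The second is that the study staff cannot follow the abstract, Table 1 and Section 2.6.3 together after week 4. Whether events in follow-up are collected depends on which text is followed.

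Safety is not the primary endpoint, but it is named in the primary objective (Section 1.2), and the Discussion promises key safety data. The comparison should therefore rest on like-for-like collection over a single stated period.

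**Working it through.** **1. The plan's own figure.** 3 sessions per week × 4 weeks = 12 sessions. This matches Section 2.5.2.

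**2. Enquiries after baseline, up to week 4.** Controls are counted at T1 and T2, where Table 1 marks safety evaluation for all participants.

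| | Tuina | Control | Extra in Tuina arm |
|---|---|---|---|
| T1 and T2 both on session days | 12 | 2 | 10 |
| T1 and T2 both on other days | 12 + 2 = 14 | 2 | 12 |

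The article does not say which case applies. If T3 to T5 also count, each arm gains three enquiries: 15 to 17 against 5.

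**3. What this could do to recorded rates (illustration only).** Nothing in the documents gives an event risk or a recall rate, so every input here except the 46 per arm and the visit spacing is an assumption. Suppose that true risk is equal in both arms, an event falls at a uniformly distributed time between two enquiries, and it is reported at the next enquiry with probability exp(−lag/τ). The mean reporting probability for enquiries L days apart is

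r(L) = (τ/L) × (1 − exp(−L/τ)),

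with L = 28/12 = 2.33 days for Tuina (evenly spaced sessions, T1 and T2 on session days) and L = 14 days for controls. For τ = 7: Tuina (7/2.33)(1 − e^(−0.333)) = 0.850; control (7/14)(1 − e^(−2)) = 0.432; ratio 1.97.

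The last two columns give the chance that a two-sided 5% test of two proportions, 46 per arm, shows a significant excess in the Tuina arm. The recorded risks are p × r(L), and the calculation uses the normal approximation with pooled variance under the null. With equal enquiry, the chance in that direction would be about 2.5%.

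| τ (days) | r, Tuina | r, control | Ratio of recorded events | True risk 20% | True risk 30% |
|---|---|---|---|---|---|
| 3 | 0.695 | 0.212 | 3.3 | 36% | 53% |
| 7 | 0.850 | 0.432 | 2.0 | 22% | 33% |
| 14 | 0.921 | 0.632 | 1.5 | 12% | 16% |
| 28 | 0.959 | 0.787 | 1.2 | 6% | 8% |

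The direction is the same in every row. The size runs from small to large with the assumed τ, so the table shows what is possible and does not estimate the bias.

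**4. The safety window.** The text that stops at the end of treatment (abstract, Table 1) and the text that continues (Section 2.6.3) differ over weeks 4 to 28: 28 − 4 = 24 weeks, and 24/28 = 86% of the trial. The conflict applies to both arms alike, so it adds nothing to the contrast in step 2.

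**5. With common-visit enquiry only.** Both arms have 2 scheduled enquiries up to week 4, or 5 over the trial if T3 to T5 are included. The difference in the number of enquiries feeding the comparison is zero.

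**The case against.** The case on the other side has several parts, and much of it stands.

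- **A comparison remains possible.** A reader might infer that event rates cannot be compared between the arms at all. The documents do not support that. Both arms attend T1 and T2, and T3 to T5 as well, and events elicited there can be compared if the source of each report is recorded. Section 2.6.3 also speaks of continuous monitoring and of documenting all events, without restricting either to one arm. That general statement does not repair the imbalance, because the only enquiry procedure described is tied to sessions and assessments.
- **The window conflict is not a source of bias.** It is tempting to cite it as a second reason to distrust the comparison. It affects both arms equally and leaves the collection period unclear; it does not favour an arm.
- **Respiratory worsening in follow-up would not go unseen.** Asthma-control and TCM symptom scores continue to T5, and an exacerbation needing emergency treatment is a withdrawal criterion (Section 2.2.3). This is correct, although these scores do not replace an adverse event record.
- **Session-level questioning is proper for tolerability.** Pain, hematoma or skin reactions to a manual therapy should be asked about when it is given, and unequal contact is inherent in an add-on therapy without a sham. This argues for keeping those reports, not for pooling them into the between-arm comparison.
- **No between-arm test of adverse events is specified.** The method of tabulation can be left to an analysis plan. The collection schedule, however, is fixed here, and an analysis can separate the reports only if their source is recorded.
- **Session may be used loosely.** Section 2.9 defines the safety set by receipt of at least one session of the assigned intervention, as if controls had sessions too. No control session schedule is given, so this does not alter the count.

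**Conclusion.** The point holds in two limited parts.

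First, as written, the plan asks Tuina children 12 to 14 times by week 4 and controls twice, so overall recorded rates of mild events are biased toward more events in the Tuina arm. The direction follows from the schedule. The size cannot be obtained from the documents: the ratios of 1.2 to 3.3 rest wholly on assumed recall and should not be quoted as estimates. Serious events are probably less sensitive to how often one asks. The control count of 2 relies on Table 1's safety marks at T1 and T2. A reader taking Section 2.6.3 alone, with follow-up meaning only T3 to T5, might infer that controls are never asked before week 8, but Table 1 does not support that reading.

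Second, the abstract and Table 1 contradict Section 2.6.3 on whether adverse events are collected from week 4 to week 28. The trial is single-center, so this is an ambiguity for one study team and does not create variation between sites. It needs reconciling but does not itself distort the comparison.

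Both deserve correction before data collection, because safety is part of the primary objective and the change is small.

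**What to change.** 1. In Section 2.6.3, have both arms asked the same adverse event question, in the same words, at the common visits T1 to T5.
2. Record on the case report form where each report arose: common visit, Tuina session or spontaneous.
3. Base the between-arm comparison on common-visit reports. List events elicited at sessions separately and descriptively for the Tuina arm, as tolerability data.
4. Mark safety evaluation at T3, T4 and T5 in Table 1, and reword the abstract so that it agrees with Section 2.6.3.

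The cost is one question at visits already scheduled, a source field on the form, and wording changes; the follow-up questionnaire becomes slightly longer. The remedy is not complete: children questioned at sessions may still report more at T1 and T2, so some imbalance will remain and should be acknowledged when the results are reported.

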### Data collection and management

2.7

Data will be recorded on case report forms (CRFs) and double-entered into an encrypted database. Missing data will be handled using multiple imputation. A Data Safety Monitoring Board will review data for safety and adherence to protocols. All electronic data will be stored using industry-standard encryption technology to prevent unauthorized access and data breaches. We will strictly control data access permissions to ensure that only authorized research team members can access this data, and passwords will be subject to regular audits to protect all access activities.

### Quality control

2.8

Before trial initiation, all research personnel will receive comprehensive training on the study protocol, standardized assessment procedures, and documentation requirements. All measurement instruments will be regularly calibrated to ensure accuracy. To maintain consistency, the same group of outcome assessors will evaluate the same participants whenever possible throughout the study. Data quality will be ensured through multiple measures: data will be recorded on standardized case report forms by independent personnel, regular data audits will be performed, and the data management team will verify data authenticity and resolve any data quality issues.

### Statistical analysis

2.9

All statistical analyses will be performed using Python (version 3.10 or higher). Data analysis will be conducted using standard scientific computing libraries, including NumPy, pandas, SciPy, and statsmodels. Data distribution will be assessed using the Shapiro–Wilk test. Normally distributed continuous variables will be presented as mean ± standard deviation (SD), while non-normally distributed data will be summarized as median with interquartile range (IQR). Categorical variables will be expressed as frequencies and percentages. A two-sided *p* value < 0.05 will be considered statistically significant.

All analyses will be conducted according to the intention-to-treat (ITT) principle, including all randomized participants in the groups to which they were originally assigned. A per-protocol (PP) analysis will also be performed including participants who complete the intervention without major protocol deviations. Safety analyses will include all participants who receive at least one session of the assigned intervention.

### Ethics approval and consent to participate

2.10

This study will be conducted in accordance with the principles of the Declaration of Helsinki. The study protocol was approved by the Ethics Committee of [Shanghai Municipal Hospital of Traditional Chinese Medicine] (Approval No.: [2025SHL-KY-102-02]). Written informed consent will be obtained from caregivers and participants aged ≥8 years. Adverse events will be reported to the ethics committee within 24 h. Results will be published in peer-reviewed journals and presented at conferences.

## Discussion

3

This study endeavors to assess the efficacy and safety of pediatric Tuina as an adjunctive therapy for CARAS in children through a randomized controlled trial. Should the trial outcomes substantiate the primary hypothesis—that the combined treatment cohort demonstrates significant enhancement over the conventional treatment group in terms of quality of life (PRQLQ score) and asthma management (C-ACT/ACT score)—the results will have substantial implications for clinical practice and research in integrative medicine.

First, at the clinical practice level, positive results would provide high-level evidence for the integrated management of CARAS. Pediatric Tuina, as a non-invasive, painless, and readily accepted external therapy, holds promise as an ideal “add-on” option. Without interfering with standard pharmacological treatment, it could synergistically improve coexisting upper- and lower-airway symptoms through TCM's holistic regulatory approach (such as ventilating the lungs, clearing the orifices, reinforcing healthy qi, and consolidating the root). This may reduce symptom fluctuations and enhance long-term treatment adherence and quality of life for affected children. Such an approach would be of significant value to families seeking alternative or complementary therapies to medication.

Secondly, at the level of academic research, this study aims to address a significant gap in the current field. Existing literature predominantly investigates interventions for allergic rhinitis or asthma separately; however, this research explicitly focuses on the syndromic entity of “one airway, one disease.” By using internationally recognized patient-reported outcome (PRO) measures and disease control tools, the findings will be positioned to align with mainstream international respiratory medicine research, thereby enhancing the comparability and credibility of TCM interventions within a contemporary medical framework. If the TCM symptom scores also show synchronous improvement, this would further support the advantage of individualized treatment plans based on syndrome differentiation in managing complex diseases.

Nevertheless, we acknowledge the limitations inherent in this study. The most prominent restriction concerns the intervention, which makes blinding of participants and operators exceedingly challenging, thereby potentially introducing performance bias and placebo effects. To partially address this issue, blinding will be implemented for outcome assessors and statisticians. Furthermore, because this study does not include biomarker detection, any observed clinical improvements will remain a “black box” regarding the underlying biological mechanisms (whether modulation of immune-inflammatory pathways is involved). Elucidation of these mechanisms will require future mechanistic exploratory trials. Additionally, although a 24-week follow-up is scheduled to evaluate mid- to long-term effects, the longevity of the intervention's benefits and its efficacy in preventing relapse in CARAS, a chronic condition, will require validation through studies with extended follow-up periods. Another limitation concerns the primary outcome measures. The PRQLQ only assesses rhinoconjunctivitis-related quality of life and does not capture the asthma component of CARAS, which constitutes a limitation of the present study. Future research should incorporate asthma-specific outcome measures, such as the Asthma Quality of Life Questionnaire (AQLQ) or lung function parameters, to enable a more comprehensive evaluation of CARAS.

In summary, this study is expected to provide key clinical effectiveness and safety data on pediatric Tuina for the treatment of CARAS. Should positive results be obtained, they would strongly promote the integration of this traditional Chinese therapy into modern comprehensive management guidelines for pediatric respiratory diseases and lay a solid foundation for subsequent research into mechanisms, protocol optimization, and health economic evaluation.
